#### Prognostic data

Information regarding oxygen therapy and exacerbations will be obtained from participants at 1- and 3-month follow-ups supplemented with information from patient files. Information regarding hospital contacts and mortality will be obtained from patient files.

### Plans to promote participant retention and complete follow-up {18b}

From previous studies among individuals with severe COPD, it has been reported that it was a challenge to recruit participants due to the burden of their clinical condition [41]. Therefore, it is important to minimize the burden for the patients and to secure a comfortable atmosphere. This study intends to have as few outcomes as possible that require physical activity from the participant, few different persons involved in patient contact, and to do all assessments as home visits. We expect this will increase the likelihood of a higher recruitment and retention rate throughout the study period. The study coordinator will be involved in every contact with the participant to secure a familiar and comfortable atmosphere. In case the study coordinator is unable to attend, it is necessary that a replacement will be arranged in agreement with the participant. The potential replacement will receive thorough training. The study coordinator is therefore involved in every step from recruitment, throughout the course of the intervention and at all visits. Participants may withdraw from the study at any time. The study coordinator will make any reasonable effort to complete the follow-up. Participants who wish to withdraw will be asked if they want to withdraw completely or partially. Partial withdrawal may be either to accept the use of their data collected prior to withdrawal or to continue without any future contact i.e. only data collection via patient files.

### Data collection for participants who discontinue or deviate from intervention protocols

Deviation from the intervention is defined as less than 6 regular contacts and an intake of less than 80% of the calculated protein or energy requirement for ≥ one third of the intervention period. Reasons for non-adherence will be registered as part of the regular contact or at follow-up visits. It is the intention to collect all data independent of deviation from the protocol.

### Data management {19}

At all visits, data will be entered directly into the electronic database REDCap (https://redcap.regionh.dk/). Though in cases with a limited internet connection or other technical issues, data will be collected on REDCap-generated case report forms and entered into REDCap as soon as possible. Access to the electronic database requires an access permit and a password.

### Confidentiality {27}

The processing of personal data will be handled in accordance with the General Data Protection Regulations. An identification number will be assigned to all included patients and all data will be handled pseudoanonymized. An identifiable list containing the project identification number will be conducted and stored in the hospital database in a network drive separately from all other project documents. The data management is estimated to end by December 31, 2025.

### Plans for collection, laboratory evaluation, and storage of biological specimens for genetic or molecular analysis in this trial/future use {33}

This project does not include the collection of biological specimens.

## Statistical methods

### Statistical methods for primary and secondary outcomes {20a}

#### Main analysis

Data on the primary outcome as well as all continuous secondary and other outcomes will be analyzed using linear mixed models that include an intervention group-time interaction as a fixed-effects term whereas between-participant variation is captured by means of (participant-specific) random (intercept) effects. There will also be random effects for the blocks used to account for the block randomization [42]. Baseline values will be part of the outcome [43].

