### Participant timeline {13}

The participant timeline is shown in Table 1 and the flow diagram in Fig. 1. All participants will have a home visit to collect data at baseline and 1 and 3 months after baseline. Enrollment began in May 2021 and is estimated to end in March 2023.

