#### Sensitivity analysis

Additionally, linear mixed models that also include relevant covariates (as fixed effects) will be fitted to adjust for observed baseline imbalance (if needed). Relevant covariates include age, BMI, sex, pulmonary function, and the number of comorbidities.

For all fitted linear mixed models, the two estimated mean changes from baseline to 3 months (for both intervention groups) as well as the estimated mean difference in change from baseline to 3 months will be reported together with the corresponding 95% confidence intervals and *p* values. Statistical significance will be declared whenever the *p*-value is below 0.05.

Where appropriate, outcome values will be transformed prior to the statistical analysis.

For categorical secondary or other outcomes data will be analyzed by means of logistic mixed-effects regression models that include an intervention group-time interaction as a fixed-effects term and block and participant-specific random effects. Baseline values will be part of the outcome. The estimated difference in change from baseline to 3 months will be reported as a ratio of odds ratios together with the corresponding 95% confidence interval and *p* value.

Statistical analyses will be carried out using STATA/IC version 17.0 (StataCorp LP, USA). Specifically, the commands XTMIXED and XTMELOGIT will be used for fitting linear mixed models (using residual maximum likelihood estimation) and logistic mixed-effects regression models (using maximum likelihood estimation), respectively.

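### The primary model's random-intercept-only covariance understates the standard error of the 0-to-3-month contrast if correlation fades over time, and the plan does not say whether the arms share one baseline mean

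*Protocol article*

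**What the plan says.** All from the protocol article.

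- **Main analysis {20a}.** The primary outcome and all continuous secondary and other outcomes are analysed by "linear mixed models that include an intervention group-time interaction as a fixed-effects term". Within participants, "between-participant variation is captured by means of (participant-specific) random (intercept) effects". In addition, "There will also be random effects for the blocks used to account for the block randomization". On the role of baseline: "Baseline values will be part of the outcome".
- **Sensitivity analysis {20a}.** For every linear mixed model, "the estimated mean difference in change from baseline to 3 months will be reported together with the corresponding 95% confidence intervals" and p values, judged at 0.05. Fitting is by XTMIXED with residual maximum likelihood. Models with covariates are held back for observed baseline imbalance. The covariates are age, BMI, sex, pulmonary function and number of comorbidities; baseline HRQoL is not among them.
- **Participant timeline {13}.** "All participants will have a home visit to collect data at baseline and 1 and 3 months after baseline".

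The article names no random slope, residual correlation structure, unstructured covariance or robust standard error. It does not say whether the two arms' baseline means are held equal or estimated separately.

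**The concern.** A random intercept with independent residuals implies the same variance at each visit and the same correlation between every pair of visits. A block effect does not relax this within a participant. The model estimates a single residual variance by pooling over the pairs 0–1, 1–3 and 0–3 months, then applies it to the 0–3 month contrast. Repeated measures often correlate less the further apart they are. If that happens here, the pooled value is too small for exactly the contrast that carries the primary p value, and the interval is too narrow.

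The second issue is precision. Randomisation makes the true baseline means equal. A model that estimates them separately by arm does not use that fact. With complete data it returns the plain difference in change scores, which is less precise than a comparison that uses the common baseline. The same model serves every continuous outcome, so both issues reach beyond EQ-5D-5L.

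**Working it through.** **Plan's own figure.** Inputs from Sample size {14}: difference 10, SD 17, power 0.8, significance level 0.05 (two-sided assumed), 20% drop-out. n per arm = 2 × (1.96 + 0.842)² × 17² / 10² = 45.4, so 46. Then 46/0.8 = 57.5, so 58 (59 from a t-based calculation). The stated 60 is reproduced. With 60 × 0.8 = 48 evaluable per arm, power is 81% (t-based).

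**Part 1: standard error of the 0–3 month contrast.** Take complete data, equal variances σ² and free baseline means.

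- Residual variance the model estimates: σ²(1 − mean ρ), the mean taken over the three visit pairs.
- What the contrast depends on: σ²(1 − ρ03).
- Model SE / true SE = √[(1 − mean ρ)/(1 − ρ03)].
- True type I error = 2 × [1 − Φ(1.96 × ratio)].

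The article gives no correlations, so all those below are assumed.

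| ρ for 0–1 / 1–3 / 0–3 months | 1 − mean ρ | 1 − ρ03 | SE ratio | Type I error, formula | Simulated |
|---|---|---|---|---|---|
| 0.60 / 0.60 / 0.60 | 0.400 | 0.400 | 1.00 | 5.0% | 5.2% |
| 0.70 / 0.65 / 0.60 | 0.350 | 0.400 | 0.94 | 6.7% | 6.9% |
| 0.75 / 0.70 / 0.60 | 0.317 | 0.400 | 0.89 | 8.1% | 8.4% |
| 0.70 / 0.50 / 0.40 | 0.467 | 0.600 | 0.88 | 8.4% | 8.7% |
| 0.70 / 0.65 / 0.50 | 0.383 | 0.500 | 0.88 | 8.6% | 8.8% |
| 0.80 / 0.70 / 0.60 | 0.300 | 0.400 | 0.87 | 9.0% | 8.9% |
| 0.80 / 0.64 / 0.512 (autoregressive, 0.8 per month) | 0.349 | 0.488 | 0.85 | 9.7% | 9.8% |
| 0.55 / 0.55 / 0.60 | 0.433 | 0.400 | 1.04 | 4.1% | not run |

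Simulations used 48 per arm and 20,000 trials (8,000 for the second row). A baseline-adjusted 3-month comparison, run alongside in five of the 20,000-trial patterns, stayed at 4.8 to 5.2%. Autoregressive decay of 0.9 per month goes a little past the table: ratio √(0.187/0.271) = 0.83, type I error 10.4%.

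**Part 2: free against common baseline means.** Let ρ be the baseline-to-3-month correlation.

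- Variance of the difference in change, relative to a follow-up-only comparison: 2(1 − ρ).
- Variance of the baseline-constrained or baseline-adjusted estimate on the same scale: 1 − ρ².
- Ratio: 2(1 − ρ)/(1 − ρ²) = 2/(1 + ρ).

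| ρ | Variance ratio | Power, free means | Power, common baseline |
|---|---|---|---|
| 0.4 | 1.43 | 74% | 88% |
| 0.5 | 1.33 | 81% | 91% |
| 0.6 | 1.25 | 89% | 95% |

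Power is t-based, with 48 per arm, difference 10 and SD 17. It therefore rests on the chronic respiratory disease questionnaire used for planning, not on EQ-5D-5L, and takes the standard error as correct. At ρ = 0.5, 2(1 − ρ) = 1, so the change contrast has exactly the planned variance. Below that it falls short of plan; above it, it does better.

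**The case against.** Several points on the other side are sound and limit what can be claimed.

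- **The inflation is conditional.** The type I error figures rest wholly on assumed correlations. With flat correlation the model is right. If the 1-month visit is the noisiest, as in the last row of the first table, it is slightly conservative. A reader might infer that this trial's interval is anti-conservative; the documents show only that it would be if correlation fades.
- **Free baseline means are not stated.** Placing baseline in the outcome vector is also how a constrained model is set up, and reporting two mean changes and their difference fits either. The source cited for that sentence is not at hand. Free means remain the ordinary reading of a group-by-time interaction, and a sensitivity analysis for baseline imbalance fits that reading, but this is an ambiguity to settle.
- **Baseline is not discarded.** It enters the outcome and the reported contrast. Under free means it is used inefficiently. For ρ above 0.5 the change contrast is still more precise than a follow-up-only comparison.
- **Exposure to chance imbalance is partial.** Given a baseline difference d, the change contrast is shifted by −(1 − ρ)d: half of d at ρ = 0.5, and 30% of it at ρ = 0.7.
- **The planned power is met at ρ = 0.5 even with free means.** The second part is an efficiency gain, not the repair of an error.
- **The point estimate is not at issue** in the complete-data, free-means case. There the covariance affects only the standard error.

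What the objection does not remove is that the article fixes the random intercept, estimator and command. The covariance issue therefore challenges a stated choice, not a detail left to a later document.

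**Conclusion.** The point holds in two parts of different weight.

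**Covariance.** The stated structure is a weak choice for unequally spaced visits with the longest interval as the primary contrast. For most fading patterns tried, the standard error is about 6 to 15% too small and the type I error about 6.7 to 9.7%; slow autoregressive decay reaches 17% and 10.4%. These figures assume complete data, equal variances and correlations that the article does not supply. The algebra is firm; whether it bites in this trial is unknown. Confidence is moderate.

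**Baseline means.** The plan should say whether they are common. If they are free, the variance is 1.25 to 1.43 times what it need be for ρ from 0.6 to 0.4. This is precision available at no cost, and leaving it unused is not a mistake in the estimate. The documents do not support saying that the plan throws baseline away or chose free means outright.

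The change should be made, mainly because it protects the primary p value against a plausible departure and loses little if correlation turns out to be flat.

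**What to change.** For continuous outcomes measured before randomisation:

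1. Replace the participant random intercept by an unstructured residual covariance over the three visits and keep the block effect. If the random intercept is retained, at least specify robust standard errors.
2. State that both arms share one baseline mean, by leaving out the group effect at baseline (a constrained longitudinal model). Make this change together with the first, because once the baseline mean is shared, the weight given to baseline depends on the covariance model.
3. Prefer this to a baseline-adjusted analysis of 3-month values alone. With 20% drop-out expected and an available-case analysis planned, the longitudinal model keeps participants without a 3-month value; a 3-month ANCOVA drops them, so the two are not strictly equivalent here.

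The cost is a sentence or two in the analysis plan and one option in the Stata command. Three visits need six covariance parameters, against two for a random intercept with independent residuals, which about 120 participants support well. No data collection changes.

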#### Sensitivity analysis

Additionally, linear mixed models that also include relevant covariates (as fixed effects) will be fitted to adjust for observed baseline imbalance (if needed). Relevant covariates include age, BMI, sex, pulmonary function, and the number of comorbidities.

For all fitted linear mixed models, the two estimated mean changes from baseline to 3 months (for both intervention groups) as well as the estimated mean difference in change from baseline to 3 months will be reported together with the corresponding 95% confidence intervals and *p* values. Statistical significance will be declared whenever the *p*-value is below 0.05.

Where appropriate, outcome values will be transformed prior to the statistical analysis.

For categorical secondary or other outcomes data will be analyzed by means of logistic mixed-effects regression models that include an intervention group-time interaction as a fixed-effects term and block and participant-specific random effects. Baseline values will be part of the outcome. The estimated difference in change from baseline to 3 months will be reported as a ratio of odds ratios together with the corresponding 95% confidence interval and *p* value.

Statistical analyses will be carried out using STATA/IC version 17.0 (StataCorp LP, USA). Specifically, the commands XTMIXED and XTMELOGIT will be used for fitting linear mixed models (using residual maximum likelihood estimation) and logistic mixed-effects regression models (using maximum likelihood estimation), respectively.

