**Methods:**

An open-label randomized controlled trial with two parallel groups. Participants are recruited from the pulmonary outpatient clinic at the Department of Pulmonary and Infectious Diseases, Copenhagen University Hospital, North Zealand, Denmark, and randomly allocated to either the intervention (intervention + standard of care) or control group (standard of care). The intervention has a duration of 3 months and combines individual nutritional care with adherence support and practical tools. It contains 4 elements including an individual nutritional plan, regular contacts, adherence support, and weight diary. The primary outcome is a difference in HRQoL (EQ-5D-5L) between the intervention and control group 3 months after baseline. Difference in functional capacity (grip strength, 30-s stand chair test, and physical activity), disease-specific quality of life (COPD Assessment Test), anxiety and depression (Hospital Anxiety and Depression Scale), nutritional parameters (energy and protein intake), anthropometry (weight, body mass index, waist, hip, and upper arm circumference), body composition (total fat-free and fat mass and indices), and prognosis (exacerbations, oxygen therapy, hospital contacts, and mortality) 3 months after baseline will be included as secondary outcomes. Data will be collected through home visits at baseline and 1 and 3 months after baseline.

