### Trial design {8}

The study is a single-center, home-based, effectiveness, registry-based randomized controlled superiority trial with two parallel groups.

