### Recruitment {15}

Participants are recruited from the pulmonary ward and the outpatient clinic at the Department of Pulmonary and Infectious Diseases, Copenhagen University Hospital, North Zealand, Denmark. Potential participants are identified in the following three ways: (1) lists of individuals with COPD followed in the pulmonary outpatient clinic, (2) hospitalized in the pulmonary ward, or (3) through visits in the pulmonary outpatient clinic. The list of individuals with COPD is generated by a person from the analysis team at the hospital from the electronic medical journal (Sundhedsplatformen, EPIC, USA) and contains individuals in contact with the pulmonary outpatient clinic within a defined period (e.g., the last 12 months) with IC-10 diagnosis codes from DJ439 to DJ449. Potential participants are chosen from the generated list using random numbers generated by the statistical program R [25]. The randomly chosen individual is screened for eligibility and participants with potential eligibility will receive a letter with information about the project. Recruitment from the list will be the primary recruitment method. If it is considered necessary to use supplemental recruitment methods, the other two methods will be used. The study coordinator will visit patients during a hospitalization in the pulmonary ward and shortly introduce the project through a short oral presentation and the information letter. Finally, the nurses from the outpatient clinic have been encouraged to hand over the information letter during visits when an individual is considered potentially eligible (BMI < 25 kg/m^2^) to participate in the project. All identified potential participants will receive a phone call from the study coordinator with further information about the project.

After receiving an oral informed consent and if the inclusion criteria are met, a home visit will be scheduled. At the first home visit, informed written consent will be obtained, baseline data will be collected, and group allocation will be revealed in the abovementioned order.

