#### Nutritional risk screening

Nutritional risk is determined using NRS2002 and MNA-SF as part of the recruitment process, at the baseline and 3-months follow-up visits. The NRS2002 is largely used in the hospital setting, whereas MNA is recommended among elderly and frail individuals. The purpose is to provide simple screening tools to detect individuals at risk of undernutrition who might benefit from nutritional support. In the NRS2002, the nutritional risk is defined by the present nutritional status and risk of impairment of present status, due to increased requirements caused by stress metabolism of the clinical condition. The NRS2002 score determines if the patient is at nutritional risk using a scoring system including information about BMI, weight loss, reduced food intake, disease severity, and age. The patient is at nutritional risk if the total score is ≥ 3 [28]. In addition, the MNA-SF is used as supplemented information on nutritional risk. MNA also determines nutritional status based on a scoring system including information on food intake, weight loss, mobility, psychological stress, neuropsychological problems, and BMI. A total score of 12–14 indicates normal nutritional status, whereas a total score of 8–11 and 0–7 indicate risk of malnutrition and malnutrition, respectively [28].

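### The 0.05 significance rule also covers each arm's own change from baseline, which does not test the intervention; it should be limited to the between-arm difference

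*Protocol article*

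**What the plan says.** The rule stands under the Sensitivity analysis subheading of Statistical methods {20a}, but its wording covers all fitted linear mixed models. By the Main analysis paragraph, these are the models for the primary outcome and for all continuous secondary and other outcomes. They report "the two estimated mean changes from baseline to 3 months (for both intervention groups) as well as the estimated mean difference in change", each with a 95% confidence interval and a p-value. The next sentence reads "Statistical significance will be declared whenever the *p*-value is below 0.05". Nothing limits it to one of the three estimates.

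Elsewhere the article treats the effect as a contrast between arms:

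- The abstract states: "The primary outcome is a difference in HRQoL (EQ-5D-5L) between the intervention and control group 3 months after baseline".
- Trial design {8} describes a "registry-based randomized controlled superiority trial with two parallel groups".
- For categorical outcomes, the same Sensitivity analysis text gives only the between-arm contrast: "The estimated difference in change from baseline to 3 months will be reported as a ratio of odds ratios".
- Subgroup effects ({20b}) are reported only as differences between subgroups in the between-arm difference in change.

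Some outcomes share content with the entry screen. Nutritional risk screening describes NRS2002 as "a scoring system including information about BMI, weight loss, reduced food intake, disease severity, and age". Weight, BMI and food intake are outcomes. The COPD Assessment Test (CAT) is an outcome too, and a CAT score of 10 or more is one way for a GOLD grade 2 patient to qualify.

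**The concern.** A within-arm p-value asks whether one arm's mean moved between baseline and 3 months. It does not ask whether the intervention moved it. Both arms may change together through usual care, the natural course, response to an open-label study with home visits, or some regression to the mean in variable measures linked to entry (24-hour recall intake and, in part, CAT). Such a shared change cancels in the between-arm difference but stays in full in each arm's own change.

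Under the rule as written, a report could call the intervention arm's change significant and the control arm's change not significant, and be within the plan. That pattern can arise by chance when the arms do not differ. In a randomised superiority trial, a result that sets aside the randomised comparison should not carry the same label as the result that uses it.

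**Working it through.** **Inputs.** From Sample size {14}: difference 10, SD 17, 60 per group, 20% drop-out, power 0.8, significance level 0.05 (taken as two-sided). The documents give no SD of change, no correlation between visits and no expected shared shift, so the shift is an assumption and is shown as a range.

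**The plan's own figure.** n per arm = 2 × (1.960 + 0.842)² × 17² / 10² = 45.4, so 46. With drop-out, 46 / 0.8 = 57.5, so 58. The t-test version needs 47, and 47 / 0.8 = 58.75, so 59. The stated 60 is consistent with both. Expected completers: 60 × 0.8 = 48 per arm.

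**Within-arm test with no treatment effect.** Let both arms shift by the same amount d, in units of the SD of the change score. With a one-sample t-test, n = 48, two-sided 0.05, the critical value is 2.012 and the non-centrality is d × √48 = 6.93d. Let p be the probability that one arm's own change is significantly improved. The arms are independent, so the intervention arm is significantly improved and the control arm is not with probability p(1 − p).

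| Shared shift d | p | p(1 − p) |
|---|---|---|
| −0.1 | 0.004 | 0.004 |
| 0 | 0.025 | 0.024 |
| 0.1 | 0.10 | 0.09 |
| 0.2 | 0.27 | 0.20 |
| 0.3 | 0.53 | 0.25 |
| 0.4 | 0.77 | 0.17 |

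The reverse pattern, control improved and intervention not, has the same probability in each row.

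**Between-arm test.** The shared shift cancels. The false-positive rate is 5% two-sided, 2.5% in the favourable direction, for every d.

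**How much shift could entry selection cause?** Suppose the lowest half of a population were selected on the baseline value itself. With correlation ρ between visits, the expected drift back is (1 − ρ) × 0.399 / 0.5 SD of the measure. The SD of change is √(2(1 − ρ)) SD of the measure (ignoring the narrowing by selection), so dividing gives the drift in the units of the table above.

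| ρ | Drift, SD of the measure | Drift, SD of change |
|---|---|---|
| 0.5 | 0.40 | 0.40 |
| 0.8 | 0.16 | 0.16 / 0.632 = 0.25 |
| 0.9 | 0.08 | 0.08 / 0.447 = 0.18 |
| 0.98 | 0.016 | 0.016 / 0.20 = 0.08 |

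This drift can matter for a variable measure and is small for a persistent one such as weight or BMI. For this trial it errs on the high side, because eligibility is judged before the baseline visit (Recruitment {15}) and not on the baseline value.

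**The case against.** The strongest reply is that the decision is already a between-arm one. The primary outcome is defined as a difference between groups, the model is built on the group-time interaction, and the between-arm estimate must appear beside the two arm-specific changes. The article calls a p-value significant; it nowhere says that a within-arm p-value will be read as efficacy. This stands. It makes the point one of wording and interpretation, and it does not fault the primary test.

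A reader might infer more: that entry picks people at a low point on the outcome measures, so that an ineffective intervention is likely to be declared beneficial. The documents do not support this, for four reasons.

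- EQ-5D-5L is not an entry criterion. A CAT threshold can apply only to GOLD grade 2, since grades 3 and 4 enter from any group.
- Entry requires a stable phase. The clinic list, sampled at random, is the main recruitment route. The ward route ("The study coordinator will visit patients during a hospitalization in the pulmonary ward") is supplementary, and baseline is measured at a home visit.
- The article also expects decline: the Discussion describes falling HRQoL, and the missing-data section names worsening as the main expected reason for missing values. A shared decline makes a false within-arm improvement rarer.
- A shared improvement of 0.2 to 0.4 SD has no source in the documents. Setting the resulting 17–25% against a 2.5% error rate would compare the trial's test with a two-p-value reading that the plan does not contain.

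It can also be said that a within-arm confidence interval shows whether zero is excluded just as a p-value does. That is true. The gain from the change is that the label of significance is kept for the randomised comparison.

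**Conclusion.** The point holds in a limited form. The text gives p-values to within-arm changes for the primary and all continuous outcomes and applies an unrestricted 0.05 rule to them. This is a stated rule, not a detail left to an analysis plan, and it is out of line with the between-arm reporting of categorical outcomes and subgroups in the same article.

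Its size depends on a shared shift that the documents do not give. With 48 completers per arm, a one-sample t-test and no treatment effect, the chance of a significant improvement in the intervention arm's own change runs from under 1% (shared decline of 0.1 SD of change) through 2.5% (no shift) to 27% and 77% (shared improvement of 0.2 and 0.4 SD). These are illustrations, not forecasts for this trial. The primary between-arm test, its error rate and the sample size are unaffected.

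**What to change.** In the Sensitivity analysis text of Statistical methods {20a}, state that significance at 0.05 is declared only for the estimated between-arm difference in change from baseline to 3 months. Report the two arm-specific mean changes with 95% confidence intervals as description, without p-values, and say that no conclusion on the effect of the intervention is drawn from them. This brings the continuous outcomes into line with the article's handling of categorical outcomes and subgroups.

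The cost is a sentence or two of analysis wording. It needs no extra data or participants and takes no power from the primary comparison.
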